## 15. Statistical analysis

The analysis sets used for the evaluation of data obtained in this clinical trial will be defined as follows:

- **Intention-to-treat (ITT) set**
  - The ITT set consists of **all participants who were randomized and received the trial intervention at least once**.
- **Full analysis (FA) set / Full analysis set (FAS)**
  - The FAS consists of all participants who:
    - were randomized, and
    - received the trial intervention at least once, and
    - have **at least one post-baseline efficacy assessment**.
  - The FAS follows the ITT principle and will be used as the **primary analysis set for efficacy**.
- **Per-protocol (PP) set**
  - The PP set includes participants who meet **all** of the following conditions:
    1. Fully satisfy the **inclusion and exclusion criteria**.

2. Have completed at least the **minimum predefined number of treatment sessions** (patients who received **5 or more** of the total 8 planned treatment sessions).
  3. Patients whose treatment was completed because they **met the predefined criteria for treatment completion due to symptom improvement**.
- **Safety analysis (SA) set**
    - The safety analysis set consists of all participants who were randomized and received the trial intervention **at least once**, and for whom **at least one safety assessment** was performed.
    - The SA set will be used for **all safety analyses**.
- 

In this clinical trial, the general principle for statistical analysis is as follows:

- All statistical tests will be **two-sided**, with a **significance level of  $\alpha = 0.05$** .
- Efficacy analyses will primarily be performed using the **full analysis set (FAS)**, with the **PP set** used as a **supplementary analysis**.
- Safety analyses will be performed in the **ITT (SA) set**, i.e., all randomized participants who received at least one treatment.

For missing data:

- For **continuous efficacy variables** in the FAS, missing values will be imputed using the **Last Observation Carried Forward (LOCF)** method, replacing missing values with the most recent available value prior to the missing time point.
- For all other variables, missing data will **not** be imputed, and analyses will be performed using the observed data as they are.

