#### ○ Early termination of the clinical trial (for a participant)

1. During the clinical trial, if symptoms improve and, based on both the participant's personal request and the judgement of the clinical trial physicians, it is determined that no further treatment is necessary, the clinical trial may be **terminated early** for that participant.
2. Participants whose clinical trial participation is terminated early for this reason are **not** included in the discontinuation/withdrawal group and are considered to have been **fully compliant with treatment**.

---

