## 10. Treatment compliance (Treatment compliance)

The clinical trial investigator (or a delegated individual) will encourage and guide participants at every visit when usual care and Chuna manual therapy related to the clinical trial are provided, so that **treatment compliance is maintained**.

Treatment compliance is calculated based on the **number of planned treatment sessions** and the **actual number of sessions received**, using the ratio of the actual number of treatments to the planned number of treatments.

After randomization, treatment compliance is considered adequate when participants have received **at least 5 out of the 8 scheduled Korean medicine treatment sessions**.

To evaluate treatment compliance, the clinical trial investigator (or delegated individual) must keep a **record of the treatments provided**.

Participants whose clinical trial participation is terminated early due to **symptom improvement** according to the early termination criteria are regarded as having been **fully compliant with treatment**.

---

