### c. Exploratory efficacy analysis

Exploratory outcomes will be analyzed as follows:

- **Additional procedures/surgery after the study**
  - ▶ Evaluation of additional nerve block procedures or surgery after the end of treatment
    - Within 8 weeks after the end of the treatment period, it will be investigated whether participants received additional procedures for pain control (e.g., **nerve block procedures**, radiofrequency ablation) or underwent **lumbar surgery**. Based on these data, the **rate of additional procedures** will be evaluated.
    - If significant differences between treatment groups are identified, **post-hoc tests** will be performed.
    - Between-group comparisons of the rates of additional procedures or surgery will be conducted using the **Chi-square test** or **Fisher's exact test**.
    - *Additional procedure rate* =  

$$\left( \frac{\text{Number of patients who underwent additional procedures or surgery}}{\text{Number of patients who completed the study}} \right) \times 100$$
- **Rate of early termination of treatment**
  - ▶ Evaluation of the early termination rate

- Among participants whose treatment was completed early because they met the predefined criteria for **treatment completion prior to the scheduled end of therapy**, the **rate of early termination** will be evaluated for each group.
  - Between-group comparisons of the early termination rate will be conducted using the **Chi-square test** or **Fisher's exact test**.
  - *Early termination rate* =  

$$\left( \frac{\text{Number of patients whose trial participation was terminated early}}{\text{Number of patients who completed the study}} \right) \times 100$$
  - **Analysis of rescue medication use**
    - ▶ Analysis of rescue medication use
      - For each participant, information on the **type of rescue medication used**, **dose**, and **timing of administration** will be collected.
      - For each treatment group, the number of uses and total amount of rescue medication by drug type will be compared between groups using an **independent t-test**, or, if the normality assumption is not satisfied, a **Wilcoxon rank-sum test**.
- 

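### The per-protocol definition makes its three conditions cumulative, so as written it admits only participants who stopped early for improvement after 5 to 7 sessions

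*Protocol*

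**What the plan says.** Protocol, Section 15 (Statistical analysis), opens the PP definition with "The PP set includes participants who meet all of the following conditions" and numbers three items. Participants must "Fully satisfy the inclusion and exclusion criteria". They must have had a minimum number of sessions, given as 5 or more "of the total 8 planned treatment sessions". The third item covers patients whose treatment ended because they "met the predefined criteria for treatment completion due to symptom improvement".

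Three other places bear on what these items mean:

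- **Section 15, c. Exploratory efficacy analysis**, defines the early termination rate through criteria for "treatment completion prior to the scheduled end of therapy".
- **Section 9, early termination for a participant**, sets the rule: "During the clinical trial, if symptoms improve and, based on both the participant's personal request and the judgement of the clinical trial physicians", no further treatment is needed. These participants are not counted as withdrawals. Item 5 of the withdrawal criteria in the same section applies the 5-session minimum only where the early termination criteria are not met.
- **Section 10** calls 5 of 8 sessions adequate compliance. It adds a second route: "Participants whose clinical trial participation is terminated early due to" symptom improvement count as fully compliant, with no minimum number of sessions.

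The full analysis set (FAS) is primary for efficacy and the PP set is supplementary. The protocol defines the PP set nowhere else.

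**The concern.** Condition 3 describes one particular way of leaving treatment early. Listed as a further requirement, it turns a set meant to represent adequate adherence into a set of people who improved enough to stop. A participant who adheres perfectly and takes all 8 sessions cannot qualify.

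Two consequences follow if the text is applied as it stands. The set would be small. It would also be conditioned on improvement after randomisation, which is close to the primary outcome itself (change in low back pain NRS). A comparison of the arms within such a set would say little about the effect of treatment in those who adhered to it.

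If the wording is instead corrected informally at the analysis stage, PP membership becomes a choice made once data are available, in a 46-participant trial where participants and treating clinicians know the allocation.

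**Working it through.** **Step 1. The plan's own numbers.** Section 6, item 3 uses d = 0.96, two-sided alpha 0.05 and 80% power. Its formula gives 2 × (1.96 + 0.84)² / 0.96² = 2 × 7.84 / 0.9216 = 17.01, rounded up to 18 per group. With 20% dropout, 18 / 0.80 = 22.5, rounded up to 23 per group and 46 in total. These figures reproduce, and the PP wording does not affect them.

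**Step 2. What condition 3 means.** The item does not itself contain the word early. The only symptom-improvement rule in the protocol is the early termination rule in Section 9, and the exploratory analysis in Section 15 places that completion before the scheduled end. A participant who takes the eighth and last session has not stopped before the end, so fails condition 3.

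**Step 3. Membership for eligible participants** (condition 1 met):

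| Sessions | Stopped for improvement | As written: 1 and 2 and 3 | 1 and (2 or 3) |
|---|---|---|---|
| 8 | no | out | in |
| 6 | no | out | in |
| 6 | yes | in | in |
| 5 | yes | in | in |
| 3 | yes | out | in |
| 3 | no | out | out |

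As written, only improvement stops after 5 to 7 sessions qualify. The row with 8 sessions contradicts Section 10, which calls 5 of 8 adequate. So does the row with 6 sessions and no improvement stop. The row with 3 sessions and an improvement stop contradicts Sections 9 and 10, which call such a participant fully compliant. The right-hand column agrees with both sections in every row.

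**Step 4. Size.** The protocol states no expected rate of early stopping for improvement, so the rate r is an assumption and is shown as a range. The upper limit for the literal set is 23 × r per arm. It is an upper limit because some improvers will stop before session 5 and fail condition 2.

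| Assumed r | 23 × r | Literal PP set per arm, at most about |
|---|---|---|
| 5% | 1.15 | 1 |
| 10% | 2.3 | 2 |
| 20% | 4.6 | 5 |
| 30% | 6.9 | 7 |

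For comparison, 23 × 0.80 = 18.4, or about 18 per arm after the planned dropout. No power is quoted for the small sets, because d = 0.96 was planned for the full randomised comparison and there is no reason for it to hold among people selected for having improved.

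**The case against.** The strongest reply is that the intent can be recovered. Items 1 and 2 are phrased as things a participant does, whereas item 3 switches to naming a class of patients and does not read naturally as a condition to be met. With Sections 9 and 10 in view, most statisticians would take item 3 as an alternative to item 2. The PP analysis is also only supplementary. Both points stand, and they limit the weight of the finding. They do not remove it: the text says all, no other section corrects it, and a programmer who follows it exactly obtains the wrong set.

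A reader might also infer three stronger things that the protocol does not support.

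- **That the literal set would have no observed week-4 NRS.** Section 8, item 5 assesses those who terminate early 8 weeks after their last session. For someone stopping about 2 to 4 weeks after baseline, that falls at about weeks 10 to 12. But Section 8, item 4 has all participants who pass screening attend at 4 weeks after baseline. The two conflict, so absence of week-4 data cannot be asserted.
- **That the PP analysis is the only further look at the primary outcome.** It is the only supplementary analysis set named for efficacy, but Sections 14.1 and 15 also plan a responder classification on low back pain NRS at weeks 4 and 12.
- **That the size of the literal set, or a difference in early stopping between arms, can be stated.** Neither can, because no rate is given.

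**Conclusion.** The PP definition is wrong as written. It excludes all participants who complete treatment, and it contradicts the compliance rules in Sections 9 and 10 in both directions: adequate attenders without an improvement stop are out, and so are fully compliant improvers with fewer than 5 sessions. This conclusion rests on the wording and on reading condition 3 as stopping before the scheduled end, which the exploratory section supports. It does not depend on any assumed rate.

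The size does depend on one: at most about 1 to 7 per arm for early-stop rates of 5% to 30%, against about 18. A higher rate would give a larger set, but one still selected on a good outcome.

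The consequence is confined to the supplementary efficacy analysis. The FAS analysis and the sample size are untouched. It should be corrected, but it does not threaten the trial's main result.

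**What to change.** Reword the PP definition in Section 15 so that a participant qualifies by meeting condition 1 and either condition 2 or condition 3, with condition 3 referring explicitly to the early termination rule in Section 9. Carry the same wording into the statistical analysis plan if there is one. Do this before data are reviewed.

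Do not add a requirement for an observed week-4 NRS to the PP definition at this stage. Under the early discontinuation visit in Section 8, item 5, it could remove again the early improvers whom the rewording admits. Items 4 and 5 of Section 8 must first be reconciled on when participants who terminate early are assessed.

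The cost is one sentence in a protocol amendment. The sample size, visits and data collection do not change.

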#### (2) Rationale for the number of participants in the pilot clinical study

##### ☐ Analysis of previous studies

The sample size for this study was calculated based on the results reported in a previous similar clinical study, using **Cohen's effect size**.

In the previous study, the change in low back pain NRS score in the **Chuna + usual care group** was  $3.02 \pm 1.72$ , whereas in the **usual care group** it was  $1.36 \pm 1.75$  ( $p < 0.001$ ). Based on these data, the effect size (Cohen's  $d$ ) was calculated to be  $d = 0.96$ .

Assuming a two-tailed test, significance level  $\alpha = 0.05$ , and statistical power  $(1 - \beta) = 80\%$ , the following formula was used:

$$n = 2 \times [(Z_{\{\alpha/2\}} + Z_{\beta})^2 / d^2]$$

Here,  $Z_{\{\alpha/2\}}$  is the Z value for a two-sided test at significance level 0.05 (1.96), and  $Z_{\beta}$  is the Z value for 80% power (0.84).

The calculation indicated that the **minimum required sample size per group is 18 participants**.

Taking into account an anticipated **20% dropout rate** during the study, the final target sample size was set at **23 participants per group**, resulting in a total of **46 participants** to be enrolled.

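### At week 4 the protocol's LOCF rule can only carry baseline forward, and the FAS deletes the other dropouts, so the primary estimate can be biased and 80% power is not assured

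*Protocol*

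**What the plan says.** **Analysis sets (protocol, section 15).** The set labelled ITT is "all participants who were randomized and received the trial intervention at least once". The FAS adds the condition of "at least one post-baseline efficacy assessment". The FAS is said to follow the ITT principle and is the primary efficacy set.

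**Missing data (section 15).** Continuous efficacy variables in the FAS are imputed by LOCF, "replacing missing values with the most recent available value prior to the missing time point".

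**Primary analysis (section 15, 2) a).** ANCOVA of the change in back-pain NRS from baseline to week 4, with treatment group as fixed effect and baseline NRS as covariate.

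**When NRS is measured (sections 8 and 14.1).** Weeks 0, 4 and 12. The checks listed for every treatment visit are adverse events and vital signs only.

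**Early stoppers (section 8, item 5).** Anyone who has had at least one session and then stops early attends one unscheduled visit 8 weeks after the last session. NRS may be taken by telephone. No further assessment follows.

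**Early improvers (sections 9, 10, 14.1 and 15 d).** Participants who stop because symptoms improved are regarded as fully compliant and are classified as responders.

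**Sample size (section 6, item 3).** The "minimum required sample size per group is 18 participants", raised to "23 participants per group" for a "20% dropout rate".

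**The concern.** Participants without a week-4 NRS are handled in two different ways, according to whether they are seen again. Someone assessed later stays in the FAS with a change of 0. Someone never assessed again is removed. Neither treatment reflects why the value is missing, so the primary result depends in part on who happened to return.

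The zero is implausible on the protocol's own figures, which expect mean improvements of 3.02 and 1.36 points. For a participant who stopped because of improvement, it contradicts the protocol's own classification of that person as a responder.

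The deletions are a separate problem. Treatment received and later attendance both arise after randomisation, and participants know their allocation (section 7, item 2). Someone who leaves on learning that they drew usual care alone drops out of every efficacy set, and the comparison is then no longer fully protected by randomisation.

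Power is also at stake. The sample size treats dropouts as people who simply leave, not as people who enter the analysis as zeros.

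**Working it through.** **Inputs (section 6, item 3).** Change in NRS 3.02 (SD 1.72) with Chuna and 1.36 (SD 1.75) with usual care; d = 0.96; two-sided α = 0.05; power 80%; dropout 20%; 23 per arm.

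**Step 1: the plan's own figure.** 2 × (1.96 + 0.84)² / 0.96² = 17.01, rounded up to 18. Then 18 / 0.8 = 22.5, rounded up to 23. Both figures reproduce. The pooled SD is √[(1.72² + 1.75²)/2] = 1.735, so d = 1.66 / 1.735 = 0.957. After 20% loss, 23 × 0.8 = 18.4 per arm remain, with power of 83% (normal) or 81% (noncentral t; 80.5% before rounding).

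**Step 2: what LOCF yields at week 4.** The early discontinuation visit is 8 weeks after the last session. Even after a single session at the start it falls at about week 8, and so cannot precede week 4. The only earlier NRS is baseline. Imputed change = baseline − baseline = 0.

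**Step 3: bias.** Let q₁ (Chuna) and q₂ (usual care) be the shares of the FAS given a zero, unrelated to outcome. The expected difference is (1 − q₁) × 3.02 − (1 − q₂) × 1.36 = 1.66 − 3.02q₁ + 1.36q₂. The bias is towards no effect when the shares are equal. It favours Chuna only when q₂/q₁ exceeds 3.02/1.36 = 2.2.

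**Step 4: power.** In each arm, variance = (1 − q)s² + q(1 − q)m². With q = 0.20 in both arms:
- Chuna: mean 2.416, variance 0.8 × 1.72² + 0.16 × 3.02² = 3.83.
- Usual care: mean 1.088, variance 0.8 × 1.75² + 0.16 × 1.36² = 2.75.
- Difference 1.33, SD √[(3.83 + 2.75)/2] = 1.81, d = 0.73.
- Power at 23 per arm: 70% (normal) or 68% (t). About 30 per arm would be needed for 80% (normal).

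**Step 5: dependence on who is seen later.** The protocol does not fix what share of the 20% returns after missing week 4. With k as that share, n per arm = 18.4 + 4.6k and q = 4.6k/n:

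| Share of dropouts seen later | n per arm in FAS | Difference | SD | Power (t) |
|---|---|---|---|---|
| 0% | 18.4 | 1.66 | 1.74 | 81% |
| 10% | 18.9 | 1.62 | 1.75 | 79% |
| 25% | 19.6 | 1.56 | 1.77 | 77% |
| 50% | 20.7 | 1.48 | 1.79 | 73% |
| 100% | 23.0 | 1.33 | 1.81 | 68% |

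**Step 6: unequal missingness, all seen later.**

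| Zeros in Chuna / usual care | Difference | Power (t) |
|---|---|---|
| 20% / 10% | 1.19 | 58% |
| 10% / 20% | 1.63 | 86% |
| 5% / 20% | 1.78 | 93% |

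In the last row the difference exceeds the assumed true 1.66.

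**Step 7: the planned ANCOVA.** Steps 4 to 6 ignore baseline adjustment. The protocol gives no correlation between baseline and change, so 0, 0.3 and 0.5 were assumed. Simulated ANCOVA power at 20% dropout (4,000 runs per cell) was 78%, 83% and 89% with no dropout seen later; 72%, 76% and 79% with half seen later; and 67%, 67% and 74% with all seen later.

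**The case against.** A reader might infer that 80% power is simply not delivered at 20% dropout. The documents do not support that. The deletion and the zero apply to different people: a dropout with no post-baseline assessment is outside the FAS and is never imputed. If all dropouts are of that kind, 18.4 per arm remain and power is about 81%, as planned. The cost is then possible selection, not power. The loss arises only for participants seen later without a week-4 value. The early discontinuation visit makes such cases likely, but their number is not fixed.

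A reader might also take the 58% case as the expected size. It shows one direction only. If unblinded usual-care participants are the ones who leave and are seen later, the mirror case gives 86%, and the worry becomes an estimate that can favour Chuna.

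It could be said that section 8, item 4 calls all participants who pass screening to the week-4 visit, so that early stoppers may still have a value. Where they do, no imputation occurs. But item 5 gives early stoppers a single later visit, and the two items are not reconciled.

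That imputed zeros make the standard error misleading is plausible but not shown here; in the worked case the SD rises. Carrying week 4 forward to week 12 is peripheral, because the primary model is at week 4. The missing-data rule and the analysis sets cannot be treated as matters left to a SAP, since the protocol fixes both.

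**Conclusion.** The point holds in conditional form. Two parts follow from the text alone: week-4 LOCF is baseline carried forward, and the ITT set and FAS exclude randomised participants on post-randomisation events. The bias in the primary difference follows whenever an FAS participant lacks a week-4 NRS, except where the zeros in the two arms happen to offset. Its direction depends on the balance of missing values between arms. For early improvers without a week-4 value, the rule conflicts with their status as compliant responders.

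At 20% dropout the stated 80% power is not assured: it ranges from about 81% to about 68%. That range assumes the effect and SDs of section 6, equal dropout in both arms, dropout unrelated to outcome, and an unadjusted t-test. The baseline-adjusted analysis may differ somewhat, as the simulated range shows. The point should be corrected before analysis; it does not by itself call for a larger trial.

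**What to change.** 1. Define the primary efficacy set as all randomised participants, analysed as randomised. Rename the present ITT set and FAS, or drop them.
2. Replace LOCF in the primary analysis with one of these:
   - multiple imputation by arm, using baseline and any later NRS, followed by the planned week-4 ANCOVA; or
   - a repeated-measures model of NRS at weeks 4 and 12, with the week-4 contrast as primary. With baseline as a covariate, this model takes no information from participants without any post-baseline NRS, so renaming the set would not bring them into the estimate. Multiple imputation would.
3. Keep LOCF at most as a sensitivity analysis.
4. Reconcile the missing-data rule with the sections that treat early improvers as compliant responders.

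The cost is revised wording in section 15 and a little more programming. No extra visits or participants are needed.
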